### Control arm

Depots assigned to the usual practice control arm will be asked to continue with their usual care conditions. Participants in the control depots will receive an educational leaflet at the outset detailing the importance of healthy lifestyle behaviours (ie, undertaking regular physical activity, breaking up periods of prolonged sitting and consuming a healthy diet) for the promotion of health and well-being. Control participants will be requested to complete the same study measurements as those in the intervention worksites, at the same time points. On completion of the study, control depots will be provided with all of the educational material provided to the intervention participants as part of the SHIFT programme. As the intervention will be delivered by trained personnel within our partner company, the company may choose to provide the full intervention (including the education session and health coach support) to control depots on completion of the formal trial.

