### Internal pilot

We intend to conduct an internal pilot study using the first six clusters (depots). The internal pilot will examine issues surrounding worksite and participant recruitment, randomisation, compliance to the primary outcome and retention rates at 6 months following randomisation. After this period, we will continue to the full trial if the following progression criteria are met:

All 24 depots required for the full sample size agree to take part in the study. Six depots will be selected to take part in the internal pilot (three will be randomised to the intervention arm and three to the control arm). This will demonstrate that depot recruitment and intervention delivery is on track.According to our criteria, 84 drivers will need to agree to participate in the internal pilot, based on an average of 14 participants per cluster.An average of 75% of drivers opting into the study, randomised into the intervention arm, attend the education session across the three intervention depots. This figure is based on the intervention uptake rate seen in our exploratory pre-post intervention study (87%),^20^ while also recognising that take-up rates tend to be lower when moving from an efficacy to a larger multicentre effectiveness trial.No more than 20% of participants fail to provide valid data for the primary outcome measure (activPAL-determined step counts) at baseline and at 6 months postrandomisation or withdraw/are lost to follow-up during the 6-month intervention phase. This threshold is necessary as study power requires total withdrawal or loss to follow-up of no higher than 30% during the 6-month intervention and 6-month follow-up (12 months postrandomisation).

If the final two progression criteria are not fully met, strategies to improve these metrics for the full trial will be discussed with the Trial Steering Committee and the study will progress based on recommendations from this committee.

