#### Statistical analysis: main trial

Average daily steps at 12 months will be compared by group using generalised estimating equation models adjusted for baseline values and waking wear time with an exchangeable correlation structure, which adjusts for clustering. For the primary analysis missing data will not be replaced (complete case analysis) but participants will be included in the intervention group in which their depots were randomised irrespective of the intervention actually received (modified intention-to-treat analysis). We have inflated our sample size by 30% to account for potential loss to follow-up and non-compliance with the primary outcome measure. We will compare the baseline characteristics of those who have complete primary outcome data and those who do not. A sensitivity analysis using multiple imputation will be performed to assess the impact of missing outcome data on the results found and to account for uncertainty associated with imputing data (full intention-to-treat analysis). The imputation will be carried out using the command MI in Stata. MI replaces missing values with multiple sets of simulated values to complete the data, performs standard analysis on each completed dataset and adjusts the obtained parameter estimates for missing data uncertainty using Rubin’s rules to combine estimates. The effect size will also be assessed by attendance excluding those who did not attend the full intervention (per-protocol analysis). Secondary outcomes and 6month data will be analysed using similar methodology.

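### The supplementary per-protocol analysis can drop drivers from the intervention arm only, so it compares intervention attenders with all controls

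*Protocol article*

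**What the plan says.** The section on statistical analysis of the main trial makes the primary analysis a complete-case comparison as randomised: "participants will be included in the intervention group in which their depots were randomised irrespective of the intervention actually received (modified intention-to-treat analysis". The model is "generalised estimating equation models adjusted for baseline values and waking wear time with an exchangeable correlation structure". Multiple imputation follows as a sensitivity analysis. Then comes the rule at issue: "The effect size will also be assessed by attendance excluding those who did not attend the full intervention (per-protocol analysis". Secondary outcomes and the 6-month data are to be handled in a similar way.

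The Control arm section says: "Depots assigned to the usual practice control arm will be asked to continue with their usual care conditions". It adds: "Participants in the control depots will receive an educational leaflet at the outset detailing the importance of healthy lifestyle behaviours". SHIFT materials reach control depots only once the study is over.

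The Internal pilot section sets a progression threshold for attendance: "An average of 75% of drivers opting into the study, randomised into the intervention arm, attend the education session across the three intervention depots". It cites 87% uptake in the exploratory pre-post study.

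**The concern.** A control driver cannot fail to attend a session that is not offered. The exclusion therefore removes drivers from one arm, and the article names no matching exclusion among controls. The controls who stay in include drivers who would have attended and drivers who would not. Those who complete a six-hour session may differ from those who do not in motivation, health, shift pattern or how their depot rosters them. Any such difference that bears on 12-month steps, and that baseline steps and wear time do not capture, enters the estimate as if it were programme effect.

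At stake is how the supplementary result is read. An effect among drivers who attended is easily taken as the effect of receiving SHIFT, although the comparison behind it is no longer randomised. Because secondary outcomes and 6-month data follow similar methods, the same problem may carry over to them.

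**Working it through.** **The plan's own figure.** The article gives no figure for the per-protocol analysis. Its sample size does reproduce (two-sided alpha assumed):
- Per arm without clustering: 2 × (2,919 × (1.96 + 0.8416) / 1,500)² = 59.4.
- Design effect: 1 + ((1 + 0.51²) × 10 − 1) × 0.05 = 1.580.
- 59.4 × 1.580 = 93.9 per arm, or 9.4 clusters of 10, rounded up to 10. One more as a small-number correction gives 11 clusters and 110 participants, as stated. A t-based check on 2(k − 1) degrees of freedom gives 78.0% power with 10 clusters per arm and 82.2% with 11.

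Attendance does not enter this calculation, so the point leaves it unchanged.

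**Bias of the exclusion contrast.** Let p be the share attending among those analysed, τ the effect in attenders, and D the difference in 12-month steps without the programme, would-be attenders minus would-be non-attenders, left after the model's adjustment. Write μA and μN for the two groups' adjusted means without the programme.
- Intervention attenders: μA + τ.
- All controls: p × μA + (1 − p) × μN.
- Difference: τ + (1 − p) × D.

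The bias is (1 − p) × D, and it is zero only if D = 0 or everyone attends.

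**Check of the formula.** A simulation with no true effect used 11 clusters of 10 per arm, ICC 0.05 and 2,000 runs. For D = 500, 1,000 and 1,500:
- At 75% attendance the formula gives 125, 250 and 375; the simulation gave 126, 237 and 380.
- At 87% attendance the formula gives 65, 130 and 195; the simulation gave 63, 136 and 215.
- The as-randomised contrast stayed within about 22 steps of zero.

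These values of D test the algebra only; they are not estimates for this trial.

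**Inputs for this trial.**
- Non-attendance: 25% (the pilot threshold of 75%) and 13% (100% − 87%).
- Raw attender minus non-attender gap: not in the documents. Assumed 500 to 1,460 steps/day, the upper end being half the stated SD (2,919 / 2).
- Share of the gap left after baseline adjustment: if the gap is equally present at baseline and the baseline-to-12-month correlation is assumed to be 0.5 to 0.7, then 1 − 0.7 = 30% to 1 − 0.5 = 50% remains.
- Residual D: 0.30 × 500 = 150 to 0.50 × 1,460 = 730.

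**Result.**
- At 25% non-attendance: 0.25 × 150 = 38 to 0.25 × 730 = 183 steps/day, or 2.5% to 12% of 1,500.
- At 13%: 0.13 × 150 = 20 to 0.13 × 730 = 95 steps/day, or 1.3% to 6.3%.

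**The alternative and its weak point.** If allocation acts only through attendance, the complier average causal effect is the as-randomised difference divided by p. A difference of 1,500 becomes 1,500 / 0.75 = 2,000 or 1,500 / 0.87 = 1,724. If non-attenders gain a fraction f of the effect, the as-randomised difference is pτ + (1 − p)fτ, and dividing by p gives τ × (1 + f(1 − p)/p). At p = 0.75, (1 − p)/p = 1/3. An assumed f of 25% to 50% then overstates τ by 8% to 17%, which is 125 to 250 steps on an effect of 1,500.

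**The case against.** - **The analysis is supplementary.** It comes after the as-randomised and imputation analyses, is openly labelled per-protocol, and no decision is tied to it. The economic section extrapolates differences between the trial groups, not this result. This stands. A reader might infer that the trial's main conclusion is biased, or that a roll-out decision rests on this figure; the article supports neither.
- **The article is condensed.** What counts as the full intervention, and how the per-protocol set is built and adjusted, may be set out in an analysis plan that is not shown. This stands for those details, which are not counted here. The exclusion rule itself is stated, and the control condition makes it one-sided.
- **Baseline steps are in the model.** A reader might apply the raw gap of 500 to 1,460 and arrive at 125 to 365 steps/day at 25% non-attendance. Only the residual gap biases the estimate, so those figures would need a gap of that size that baseline adjustment does not touch, such as one opening wholly after baseline. The documents give no basis for that. If non-attenders are also lost to follow-up more often, their share among completers falls and the bias shrinks.
- **Attendance is not purely the driver's choice.** All participants volunteered, sessions are held at the depot, and the process evaluation plan asks how timetabling staff found scheduling them. Rostering may therefore drive attendance. This stands, and it leaves even the sign of the residual difference open. It does not remove the bias, because rosters may also bear on steps.
- **The complier estimate has its own assumptions.** Champions coach intervention participants and step challenges run across intervention depots, so non-attenders may be reached. The process evaluation also expects possible contamination of controls. This stands. The estimate should not be presented as identified by design alone. In its favour, the Fitbit and the cab-workout equipment are handed out at the session.

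**Conclusion.** The point holds for the supplementary analysis. As stated, it compares a selected part of the intervention arm with the whole control arm. It estimates the effect in attenders only under the untestable condition that attendance is unrelated to 12-month steps given baseline steps and wear time. To say that it cannot estimate that effect at all would go too far.

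The size is illustrative: about 38 to 183 steps/day at 25% non-attendance and 20 to 95 at 13%. It rests on an assumed raw gap, an assumed correlation, and a gap already present at baseline; it would be larger if the gap opens later. The weight is moderate: the primary modified intention-to-treat analysis and the sample size are untouched, but the change is cheap and gives a better-founded answer to the same question.

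**What to change.** Add a complier average causal effect estimate: depot allocation as the instrument for attendance at the education session, two-stage least squares, the same baseline covariates, and cluster-robust standard errors with a small-sample correction. Include every driver with outcome data in the arm to which the depot was randomised.

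State two assumptions beside it:
- Allocation acts only through attendance. Say that this is doubtful because champion support and step challenges may reach non-attenders, and show the estimate with non-attenders assumed to gain 25% to 50% of the effect.
- Controls receive none of the programme during the trial. Check this against the contamination logs and focus groups already planned.

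Keep the exclusion analysis only as exploratory, labelled as a non-randomised comparison, and apply the same labelling where it is repeated for secondary outcomes or 6-month data.

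The cost is a change of wording and a few lines of code. The attendance logs are already in the process evaluation plan, so no new data are needed. The price is a wider interval, roughly 1/p times the as-randomised one (1.33 at 75% attendance, 1.15 at 87%), and reliance on the exclusion restriction.

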#### Qualitative analyses

Audio-recordings of interviews and focus groups with drivers, worksite champions, HR staff, health and safety personnel and logistics timetabling and planning staff will be transcribed verbatim and analysed using framework analysis,^68 69^ using the RE-AIM framework^67^ as the overarching framework.

#### Cost-effectiveness

The economic analysis will consist of a cost-consequence analysis based on the observed results within the trial period and a cost-effectiveness analysis where differences between groups in the trial will be extrapolated to the longer term. For both analyses, costs in both arms will be estimated from a NHS and Personal Social Services perspective (consistent with that used by the National Institute for Health and Care Excellence) as well as a wider public sector perspective. In each analysis, the cost of the SHIFT arm will include an estimate of the cost of the intervention (including the cost of training the educators), generated through a staff questionnaire completed at the end of each education session.

##### Within-trial analysis

Within the trial, resource use estimates will be collected from participant questionnaires and will include health-related resource use as well as absence from employment. The health-related resource use will be based on a variant of the Client Service Receipt Inventory and will include services that this population are likely to use such as GPs and practice nurse appointments, occupational health visitors and counsellors. Costs of resources will be calculated by applying published national unit cost estimates (eg, NHS reference costs or Personal Social Services Research Unit costs of health and social care),^70 71^ where available, to estimates of relevant resource use.

A range of outcomes will be assessed in the trial including health-related quality of life, measured using the EQ5D.^65^ The within-trial analysis will present incremental results for the primary and secondary outcomes (including EQ5D) in both intervention and control arms and will be compared with the incremental costs measured. We will also present the results in terms of the differences between the groups in time absent from work. Two analyses will be conducted, one including these productivity losses, the other excluding them. This will allow decision makers to assess the importance of inclusion of these costs in the adoption decision.

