**Trial registration number:**

ISRCTN10483894.

Strengths and limitations of this studyTo our knowledge, this is the first randomised controlled trial to examine the impact of a multicomponent intervention targeting individual and environmental barriers faced by heavy goods vehicle drivers to lead a healthy lifestyle.The trial will involve a full process evaluation and an economic evaluation.The primary outcome, physical activity, will be objectively measured.Sustainability of the intervention will be examined at 6 months follow-up, following completion of the intervention.Due to the nature of the intervention, participants will not be blinded to their treatment arm, and there is a risk that the secondary outcome self-report measures may be susceptible to reporting bias.

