### Sample size

Our earlier exploratory pre-post study revealed that on average HGV drivers achieve 8786 steps/day across both workdays and non-workdays with a SD of 2919 steps.^20^ We have powered this study to look for a difference in step counts (the primary outcome) of 1500 steps/day (equivalent to approximately 15 min of moderately paced walking) between the intervention group and control group. Evidence demonstrates a linear association between step counts and a range of morbidity and mortality outcomes, as well as with markers of health status including inflammation and adiposity, insulin sensitivity and HDL-C in adults.^24–26^ The linear association between step counts and health outcomes indicate that regardless of an individual’s baseline value, even modest increases in daily step counts can yield clinically meaningful health benefits. For example, a difference in daily steps of 1500 steps/day has been associated with around a 5%–10% lower risk of all-cause mortality and cardiovascular morbidity and mortality in the general population and in those with a high risk of type two diabetes, respectively.^27 28^ The proposed level of change has been chosen based on findings from our exploratory pre-post intervention,^20^ while also being clinically meaningful.

Based on a cluster size of 10, a conservative ICC of 0.05 (as there is no previous data to inform this, we have been informed by recommendations of Campbell *et al*^29^), an alpha of 0.05, power of 80% and a coefficient of variation to allow for variation in cluster size of 0.51 (based on partner company data), we will require 110 participants from 11 clusters per arm. From experience in conducting such studies, it is estimated that retention and compliance rates will be approximately 70% at 12 months follow-up; therefore, the sample size will be inflated by 30% to ensure we have adequate power in our final analysis. We will also inflate the number of clusters by two to allow for whole cluster drop out. We will therefore recruit 24 clusters with an average of 14 participants per cluster.

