##### ​Work-related psychosocial variables and mental health

A series of self-report measures will be employed to characterise work-related health and mental health: musculoskeletal symptoms will be assessed using the Standardised Nordic Questionnaire^55^; work engagement (characterised by vigour, dedication and absorption) will be measured using the Utrecht Work Engagement Scale^56^; occupational fatigue will be measured using the Occupational Fatigue Exhaustion Recovery 15 scale^57^; job performance^58^ and job satisfaction^59^ will be measured using single-item 7-point Likert scales; sickness presenteeism will be assessed using a single-item questionnaire; participant’s perceptions of work demand and support will be assessed using four subscales from the Health and Safety Executive Management Standards Indicator Tool,^60^ and driving-related safety behaviour will be assessed using a 6-item measure.^61^ Anxiety and depression will be measured using the Hospital Anxiety and Depression Scale,^62^ and social isolation will be assessed using the 8-item Social Isolation short form from the Patient-Reported Outcomes Measurement Information System.^63 64^ Data on sickness absence will be collected via self-report and employer records and will include frequency and duration of self-certified and certified sickness. Data on sickness absence will be collected from organisational records for 12 months prior to the intervention and for the 6-month intervention and follow-up periods.

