##### Long-term analysis

It is acknowledged that although there may be short-term health benefits from the intervention, the long-term effects of, for example, increased physical activity on diabetic status and number of cardiovascular events may be more important. We will therefore conduct a brief literature review to identify existing models that link short-term end points (including physical activity) measured in the trial and long-term quality of life. We have identified and used existing models^72^ linking physical activity to quality-adjusted life years (QALYs) previously. These models will be used to extrapolate costs and effects of the intervention beyond the trial period to a more appropriate time horizon. If appropriate an incremental cost-effectiveness ratio for the extrapolated period will be reported using the QALY. As with the within-trial analysis, we will conduct analyses where productivity losses are included/excluded to assess the impact on decision making. Costs and effects will be discounted at the prevailing recommended rate (currently 1.5% per annum on both costs and effects), but will be the subject of sensitivity analysis to reflect the ongoing uncertainty around appropriate discount rates for public health interventions. To reflect the levels of uncertainty in parameter inputs we will conduct probabilistic sensitivity analyses; this will allow a characterisation of the uncertainty around the adoption decision which we will depict using cost-effectiveness acceptability curves. Sensitivity analyses will be performed to determine the robustness of the results to altering certain assumptions such as the discount rate or inclusion/exclusion of productivity losses.

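### Work absence for the economic analysis is taken from unblinded drivers' questionnaires, although employer sickness records are also collected and should be the primary source

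*Protocol article*

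**What the plan says.** The Within-trial analysis section of the Protocol article names one source for absence: "resource use estimates will be collected from participant questionnaires and will include health-related resource use as well as absence from employment". It then makes absence a reported result: "We will also present the results in terms of the differences between the groups in time absent from work". Two analyses follow, one counting productivity losses and one not, so that decision makers can judge how much these costs matter. The Long-term analysis section carries this forward: "we will conduct analyses where productivity losses are included/excluded to assess the impact on decision making".

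The section on work-related psychosocial variables and mental health describes a second source: "Data on sickness absence will be collected via self-report and employer records and will include frequency and duration of self-certified and certified sickness". The records are to be "collected from organisational records for 12 months prior to the intervention and for the 6-month intervention and follow-up periods". Neither this section nor the cost-effectiveness sections give the records a part in the economic analysis or say which source leads.

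Three other places bear on the point. The strengths and limitations list acknowledges the lack of blinding and concedes that "there is a risk that the secondary outcome self-report measures may be susceptible to reporting bias". The Measurements and resource-use sections have questionnaires completed at baseline, 6 and 12 months, at assessments held in the depots; the participant recruitment section has Transport Managers schedule those visits. The Sample size section says "it is estimated that retention and compliance rates will be approximately 70% at 12 months follow-up".

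**The concern.** For sickness absence the trial will hold two measures of the same quantity, and the economic analysis names the one more exposed to bias.

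Self-report depends on the memory of drivers who know their arm. It also depends on the driver being at the depot for the assessment. A driver on long-term sick leave on that date is plausibly less likely to attend, and missingness would then depend on the quantity being measured. That is an inference from where and how visits are held; the article does not state it. Employer records depend on neither recall nor attendance.

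The planned handling of missing data does not remove the problem. The Statistical analysis section uses complete cases for the primary analysis, with multiple imputation as a sensitivity analysis, and similar methods for secondary outcomes. Imputation does not correct misreported days. In its standard form it also does not correct missingness driven by the unobserved absence itself.

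At stake are the between-arm difference in time off work and the productivity-loss version of the economic results. Absence is typically skewed, so a few long spells can carry much of the mean.

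**Working it through.** **Plan's own figures.** The article states no absence rate, no expected difference in absence and no questionnaire-completion rate, so there is no absence figure to reproduce. The sample size was set on steps/day and is not affected.

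**Step 1: how many drivers could lack 12-month self-report.** Inputs from the Sample size section: 24 clusters, average 14 drivers, about 70% retention and compliance.
- Planned drivers: 24 × 14 = 336.
- Expected with data: 336 × 0.70 = 235.2, about 235.
- Without data: 336 − 235 = 101.

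This is an upper bound for questionnaires. The Statistical analysis section ties the 30% to loss to follow-up and to non-compliance with the primary outcome measure, that is, the activPAL. A driver who attends and fills in the questionnaire but gives invalid monitor data counts in the 30% without being missing here.

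**Step 2: selective non-attendance (all absence inputs assumed).** Let a share p of an arm have a long absence of 40 days and the rest 4 days, with p = 0.10 in control and 0.05 in intervention. Overall retention is 70% in each arm, and a share q of the long-term absent is retained.
- True mean = 40p + 4(1 − p). Control: 4.0 + 3.6 = 7.6. Intervention: 2.0 + 3.8 = 5.8. Difference: 1.8 days.
- Questionnaire mean = [40pq + 4(0.70 − pq)] / 0.70.

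| q | Control | Intervention | Difference |
|---|---|---|---|
| 0.70 | 7.60 | 5.80 | 1.8 |
| 0.50 | (2.0 + 2.6)/0.70 = 6.57 | (1.0 + 2.7)/0.70 = 5.29 | 1.3 |
| 0.30 | (1.2 + 2.68)/0.70 = 5.54 | (0.6 + 2.74)/0.70 = 4.77 | 0.8 |

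With the same q in both arms, a real difference is attenuated. It is not reversed.

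**Step 3: recall (assumed).** Take a true mean of 6 days in both arms and let each arm report a share of its days. Apparent difference, control minus intervention = 6 × (control share − intervention share).
- Intervention 80%, control 90%: 6 × 0.10 = 0.6 days.
- Intervention 70%, control 90%: 6 × 0.20 = 1.2 days.
- Intervention 90%, control 80%: 6 × (−0.10) = −0.6 days.
- Equal shares: 0.

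Recall produces a spurious difference only if it differs by arm, and then in either direction.

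**The case against.** The best defence is that the economic section does not exclude the records, and that ranking and reconciling two sources is commonly left to an analysis plan not shown here. The part about ranking stands: silence on a hierarchy would not be a finding in a condensed article. But the economic section is not silent. It names a source for absence, and that source is the questionnaire. A reader might go further and infer that the records have been ruled out; the text does not support that.

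Several limits also stand. Only an absence overlapping the visit prevents attendance; a driver who was off for weeks and has returned can still report it. The reporting-bias risk is disclosed. Results are always shown without productivity losses, which bounds the consequence. The economic section speaks of absence from employment, whereas the records cover sickness absence, so the two quantities need not coincide.

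A reader might also infer that losing a few long absences would reverse the sign of the arm difference. Three 60-day absences lost from one arm of 12 × 14 = 168 do amount to 3 × 60/168 = 1.07 days per driver. That assumes the loss falls wholly on one arm, and it divides by all 168 drivers although some would have no questionnaire. Nothing in the article supports a one-sided loss.

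**Conclusion.** The point holds as a stated choice of the weaker source for sickness absence. Unblinded recall and depot-based questionnaires may bias absence, and with it the productivity-loss results. The article does not show that they will, and neither size nor direction can be derived from it.

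The only count it supports is an upper bound of about 101 of 336 drivers without 12-month self-report. It would be wrong to read this as an expected number, since no questionnaire-completion rate is given. The 0.8 to 1.3 days in place of 1.8, and the spurious 0.6 or 1.2 days, show only how the two mechanisms work under assumed inputs. A sign reversal is not demonstrated.

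The matter concerns a secondary outcome and the economic results; the primary outcome is unaffected. It is worth changing because the better source is already being collected.

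**What to change.** Reconcile the psychosocial-outcomes section with the cost-effectiveness sections:
- Name employer records as the primary source for sickness absence (days and episodes), both as the secondary outcome and for productivity losses in the within-trial and long-term analyses.
- Adjust for each driver's record over the 12 months before the intervention.
- Include drivers who missed visits, up to their leaving date, where access to their records continues.
- Keep self-report as a sensitivity analysis and for absence the records do not capture.

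Both sources are already in the plan, so the change is one of wording and needs no new data collection. The downside is that records cover sickness absence only and stop when a driver leaves the company, so self-report is still needed as a supplement. Fixing the source in advance also removes any later choice between two unranked measures.
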